**2. Goals and planning**			
2.1 Does the app ask for willingness for behaviour change?	0		
2.2 Does the app allow for the setting of goals?	1	Setting of weekly exercise goal (between 1–7 exercise sessions/week)	
2.3 Does the app have the ability to review goals, update, and change when necessary?	1	Ability to change weekly exercise goal under the profile tab at any stage	
**3. Feedback and monitoring**			
3.1 Does the app give the user the ability to quickly and easily understand the difference between current action and future goals?	1	Via the graph of weekly exercise days plotted relative to the exercise goal	
3.2 Does the app have the ability to allow the user to easily self-monitor behaviour?	1	Via the graph of weekly exercise days plotted relative to the exercise goal	
3.3 Does the app have the ability to share behaviours with others (including social media or forums) and/or allow for social comparison?	0		
3.4 Does the app have the ability to give the user feedback—either from a person or automatically?	1	Automatic feedback via personalised messages in response to the user inputting data about - the weekly number of exercise sessions achieved - the main exercise barrier encountered (if the exercise goal was not achieved)	
3.5 Does the app have the ability to export data from app?	0		
3.6 Does the app provide a material or social reward or incentive?	1	Positive reinforcement/congratulations are provided when the weekly exercise goal is reached or exceeded	
3.7 Does the app provide general encouragement?	1	Visual encouragement provided via - the graph where weekly exercise days are plotted relative to the weekly exercise goal - the home tab where progress each week is logged against a visual target (the weekly exercise goal) Text-based encouragement is provided within all exercise facilitator messages (user receives 2/week during weeks 1–4; 1/week during weeks 5–16; 1/fortnight during weeks 17–24)	
**4. Actions**			
4.1 Does the app have reminders and/or prompts or cues for activity?	1	Weekly reminders provided to log exercise sessions Regular facilitator messages prompt exercise behaviour (user receives 2/week during weeks 1–4; 1/week during weeks 5–16; 1/fortnight during weeks 17–24)	
4.2 Does the app encourage positive habit formation?	1	Habit formation BCT encouraged in week 8 and week 24 facilitator messages Habit formation targeted in two exercise barrier response messages^†^	Facilitator message: Research shows that people who integrate exercise into their daily lives find it easier to exercise long term. Research also shows people see greater improvements the longer they exercise. The aim is to try make exercise a life habit ‘I forgot to do my exercises’ barrier response message: It can be hard to remember. We suggest making the exercises a habit. Set aside the same time each day to do them. It’s much harder to forget when something is a daily routine
4.3 Does the app allow or encourage for practice or rehearsal, in addition to daily activities?	1	Ability to log more exercise sessions than the goal each week (up to 7 sessions over 7 days)	
4.4 Does the app provide opportunity to plan for barriers?	1	Barriers addressed if weekly exercise goal not met by:—user being asked to reflect on and select their major barrier to exercise for that week - based on the barrier selected, a targeted BCT message is then sent with suggestions for overcoming the specific barrier	
4.5 Does the app assist with or suggest restructuring the physical or social environment?	1	Environmental restructuring is adressed in 10 barrier response messages (in response to the user selecting the barrier ‘forgot’) ^†^	‘I forgot to do my exercises’ barrier response message: It can be hard to remember to exercise. Try putting your exercise equipment somewhere you will see it every day, this can help trigger your memory to do your exercises
4.6 Does the app assist with distraction or avoidance?	1	Distraction BCT targeted in five barrier response messages (in response to the user selecting the barrier ‘boring’ or ‘pain limits’)^†^	‘I found the exercises boring’ barrier response message: Doing the same exercise again and again can be a drag. Try distracting yourself. What about doing your exercises while watching your favourite TV show?
**Total score (out of 21)**	**17**		

*BCT* behaviour change technique

^†^Note- users do not necessarily receive all barrier response messages containing BCTs. Barrier response messages are only sent in response to specific barriers selected by users reporting < 3 exercise sessions in a week (low adherence)

^*^Note in this RCT, participants are instructed to set a weekly exercise session goal of 3 sessions and to set the length of the program for 24 weeks

For this trial, participants are instructed to input an exercise goal of three sessions per week and set the program for 24 weeks. Each week, participants receive a notification prompting them to enter the app and record how many exercise sessions they completed in the prior week. Participants also have the option of logging their exercise sessions in real-time. A graph tab displays exercise sessions completed each week so participants can monitor their progress. If participants have not achieved the goal of three sessions/week, the app asks them (weekly up to week 9 and fortnightly thereafter) to select their major exercise barrier from a predefined list (based on our research into the major barriers to exercise in OA [18]) and then sends behaviour change messages tailored to the selected barrier to help them adhere to their exercise program. Irrespective of goal attainment, the app sends extra messages throughout the week to remind and facilitate users to achieve their exercise target.

### Outcome measures

Table 4 lists the outcome measures in this RCT, relative to the timing of enrolment and interventions. The primary and secondary outcomes are collected on a web-based platform (REDCap™) or via post (if participants prefer paper versions of the questionnaires). The primary end-point is 26 weeks post-randomisation (for primary and secondary outcomes) and the secondary end-point is 14 weeks (for primary outcomes only). To encourage participant retention in the trial and completion of outcome measures, participants who complete the electronic survey at 26 weeks will be provided with a $AUD50 gift voucher to compensate them for the time they have invested in the trial.

**Table 4 Tab4:**
[figure not shown]
Schedule of enrolment, interventions and assessments

### Primary outcomes

There are two primary outcomes for this RCT:i)*Number of days strengthening exercises were performed in previous fortnight (exercise adherence)*At 14 and 26 weeks, participants are asked “In the past two weeks, how many days did you perform the strengthening exercise program your physiotherapist prescribed for your knee problem?” Options range from “0” to “6 or more”. To aid interpretation of descriptive data, responses will also be converted into a percentage of the prescribed six sessions, where 100% = exercises completed on 6 or more days of the past fortnight.ii)*Physical function over the past week*

Physical dysfunction is measured via the Western Ontario and McMaster Universities (WOMAC) Osteoarthritis Index (Likert version 3.1) [47]. It is a valid, reliable and responsive self-reported OA-specific tool [48]. The physical function subscale has 17 questions which evaluate knee function over the prior week during a variety of daily activities (response options ranging from ‘no dysfunction’ to ‘extreme dysfunction’). Total score ranges from 0 to 68 and higher scores indicate poorer function. Change scores will be determined with data from baseline, 14 weeks and 26 weeks.

### Secondary outcomes

A range of secondary outcomes are being collected at baseline and 26 weeks (unless otherwise indicated). For continuous secondary outcome measures (excluding the Exercise Adherence Rating Scale (EARS), see below), change scores will be calculated using data from baseline and 26 weeks.i)*Knee pain during walking*Average pain on walking (over the prior week) is measured with an 11-point numerical rating scale that has terminal descriptors of ‘no pain’ (score = 0) and ‘worst pain possible’ (score = 10).ii)*Sport and recreation function*The Knee Injury and Osteoarthritis Outcome Score (KOOS) [49] sport and recreational activities subscale measures function in sports and recreational activities. It comprises five questions ascertaining function with sport and recreational activities over the last week, with 5-point Likert response options ranging from ‘none’ to ‘extreme’. Total score ranges from 0 to 100, with lower scores indicating more difficulty with sports and recreational activities.iii)*Knee-related quality of life*The KOOS [49] quality of life subscale measures knee-related quality of life. It asks four questions about knee-related quality of life over the previous week, with 5-point Likert response options. Total score ranges from 0 to 100, with lower scores indicating poorer quality of life.iv)*Physical activity*Physical activity over the prior week is measured via the Physical Activity Scale for the Elderly (PASE) [50]. It comprises 10 questions about frequency and duration of recreational, household and occupational physical activity over the prior 7 days. Total scores range from 0 to 793 and higher scores are indicative of more physical activity.v)*Exercise self-efficacy*The Self-Efficacy for Exercise Scale [51] measures self-efficacy expectations about ability to continue exercising in the face of perceived barriers. This 9-item tool has scores which range from 0 to 90, with higher scores indicating better exercise self-efficacy.vi)*Participant-perceived global changes*At 26 weeks, participants rate their global change from baseline in i) knee pain, ii) physical function, and iii) their knee overall, via individual 7-point Likert scales (ranging from “much worse/less” to “much better/more”). On each scale, participants who are moderately better or much better will be classed as improved and the rest as not improved.vii)*Satisfaction with exercise program (including the mobile app, if applicable)*At 26 weeks, satisfaction with the entire exercise program (including the mobile app for those who were randomised to receive it) is rated with a 7-point Likert scale (ranging from “extremely unsatisfied” to “extremely satisfied”). Participants who are moderately satisfied or extremely satisfied will be classed as satisfied and the rest as not satisfied.viii)*Exercise Adherence Rating Scale (EARS)*A secondary measure of exercise adherence is included (in addition to the primary adherence measure). At 26 weeks, participants rate their adherence to their prescribed home strengthening exercises using Section B of the EARS [52]. This has six items and each is scored with a 5-point scale (terminal descriptors of ‘strongly agree’ to ‘strongly disagree’). The total score ranges from 0 to 24, with higher scores indicating better adherence.ix)*Willingness to undergo knee joint replacement*

At baseline and 26 weeks, participants will answer the question “How willing are you to have a knee joint replacement on your knee in the near future?” using a 5-point Likert scale (ranging from “definitely not willing” to “definitely willing”). Participants will be dichotomised into those not willing (definitely not willing; probably not willing) or willing/unsure (unsure; probably willing; definitely willing).

### Other measures

Other outcomes that will be measured for descriptive purposes, include:i)*Sample characteristics*Variables measured at baseline include; height; weight; age; gender; ethnicity; symptom duration; residential postcode; education level; employment status; comorbidities (Self-Administered Comorbidity Questionnaire [53]); treatment outcome expectations (5-point ordinal scale from “no effect at all” to “complete recovery”); confidence using technology in daily life (rated on a 4-point Likert scale with options of not at all confident, somewhat confident, moderately confident and extremely confident) and use of technologies for health (over the previous month) rated as yes or no for each of i) searching the internet for health information; ii) using an app to manage health; iii) social networking (eg Facebook, Twitter) for health information/support; iv) wearable devices/ trackers for managing health; v) following/watching YouTube for health information and/or; vi) subscription to online health management programs.ii)*Co-interventions*At baseline and 26 weeks, participants will complete a custom table to indicate how often over the prior month they used different pain and arthritis medications and other co-interventions (including use of healthcare apps) for their knee pain. Participants who used a drug/supplement at least once a week will be classed as a current user of the relevant medication. Participants who used any other co-intervention once in the past month will be reported as a recent user.iii)*Adverse events*Adverse events are considered to be “any problem experienced in the study knee or elsewhere in the body deemed by the participant to be a result of participating in the trial AND at least one of i) that caused increased pain and/or disability for two days or more, and/or ii) resulted in the participant seeking treatment from a health professional” [33]. Adverse events will be established using survey questions to participants at 26 weeks. As the interventions in this trial are low-risk, serious adverse events (incapacitating, life-threatening, hospitalisation or death) are extremely unlikely and a Data & Safety Monitoring Committee is not required.iv)*Process measures- exercise plus app group only*A range of self-reported process measures will be collected from the exercise plus app group only at 26 weeks. These include: i) downloads of the ‘My Exercise Messages’ app; ii) number of people who stop using the app (and reasons why); iii) number of days the app was used in the prior 14 days (via monthly survey until 26 weeks); iv) usefulness of the app; and v) user engagement, functionality, information quality and perceived impact of the app using the user Mobile Application Rating Scale [54].v)*Process measure- both groups*

At baseline and 26 weeks, all participants will answer the question “How effective do you believe exercise is for managing knee osteoarthritis?” using a 4-point Likert scale (with response options of “not at all effective”; “somewhat effective”; “moderately effective”; and “highly effective”).

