### Randomisation, blinding and allocation concealment

Participants are enrolled in the trial once they have given informed consent and completed the baseline questionnaire. The randomisation schedule (allocation in a 1:1 ratio to either i) exercise or ii) exercise plus app) was prepared by an independent biostatistician (permuted random block sizes), stratified by physiotherapist. The randomization schedule is stored securely online with password-protection (REDCap™) and maintained by a researcher who does not recruit participants or administer outcome measures. The same researcher reveals group allocation after baseline assessment. At this point, allocation is revealed only to this researcher. Another researcher reveals allocation to those randomised to the exercise plus app group approximately two weeks later, after the participant has completed their physiotherapy consultations (to ensure physiotherapist blinding, see below).

As this is a pragmatic trial, participants are not blinded to group allocation. However, limited disclosure is used to reduce the risk of participants allocated to the exercise only group from searching for and downloading the ‘My Exercise Messages’ app. Participants in the trial are told the trial is assessing an “exercise app” but they are not told the name of the specific app under investigation nor its specific functions or purpose. As the primary and secondary outcomes are self-reported, and participants are not blinded, by default the assessors of these outcomes are not blinded. The physiotherapists who provide the exercise programs in both trial arms are blinded to group allocation. Participants in the exercise plus app group are not told of their group allocation until after they have completed their two physiotherapy sessions, to ensure they do not disclose their group allocation to their physiotherapist. The statistical analysis plan will be written and published while the biostatisticians are blinded. Main statistical analyses will be undertaken blinded to group name.

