### Sample size calculations

A sample of 182 (91 per arm) is necessary to detect a minimum important difference of 1.2 sessions in the adherence primary outcome (number of days strengthening exercises performed in previous fortnight) at 26 weeks between groups (based on data from our trial evaluating SMS behaviour change messages [27]) with 80% power and an alpha of 0.025 (alpha of 0.05 split between the two primary outcomes), assuming a between-participant SD of 2.4 [27] and 15% attrition [28]. This sample size ensures more than 80% power to detect the minimal important difference on the clinical primary outcome of 6 units in change (follow-up minus baseline) in physical function on WOMAC [55] between the two arms, assuming a between-participant SD of 12 units [28], a baseline to 26-week correlation of 0.5 [28], an alpha of 0.025 and 15% attrition [28]. Physiotherapists treat participants in both groups, thus we have not modified the sample size for physiotherapist clustering.

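### Adverse events rest on one 26-week survey and the unblinded participant's own attribution, which risks under-capture and arm-dependent counts in the descriptive safety comparison

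*Protocol article*

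**What the plan says.** All of this is in the protocol article.

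- **Method and timing** (Other measures, adverse events): "Adverse events will be established using survey questions to participants at 26 weeks". The text shown names no other route. The schedule in Table 4 is not shown.
- **Definition** (same item): a problem counts when it is "deemed by the participant to be a result of participating in the trial AND at least one of" two further conditions, namely one "that caused increased pain and/or disability for two days or more, and/or ii) resulted in the participant seeking treatment from a health professional". Attribution is therefore necessary but not sufficient.
- **Blinding** (Randomisation, blinding and allocation concealment): "As this is a pragmatic trial, participants are not blinded to group allocation".
- **Existing contacts.** Both arms answer a questionnaire at 14 weeks, but under Outcome measures "the secondary end-point is 14 weeks (for primary outcomes only"). A monthly survey on app use goes to the app arm only (Other measures, process measures).
- **Attrition** (Sample size calculations): 15%, with 182 participants, 91 per arm.
- **Role of the data**: adverse events are listed among measures taken for descriptive purposes, and the interventions are described as low-risk.

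**The concern.** Three features act together. First, a flare of two or three days in month two has to be remembered in month six. Second, whoever does not return the 26-week survey gives no answer to the only adverse-event questions described, and people who stop because of pain may be among them. Third, a participant who knows the allocation decides whether the event is a result of the trial before it can be counted. After the second consultation the app arm has up to 24 weeks of trial prompts, while the exercise arm has no further physiotherapist support. The same flare could be blamed on the trial more readily in one arm than in the other.

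At stake is the by-arm safety description. A low count could reflect forgetting or non-attribution, and a difference or similarity between arms could reflect attribution rather than events. No efficacy result depends on it.

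**Working it through.** **1. The planning figures.** The article gives a difference of 1.2 sessions, SD 2.4, power 80% and alpha 0.025 (two-sided assumed).

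n per arm = 2 × (2.241 + 0.842)² × (2.4/1.2)² = 2 × 9.505 × 4 = 76.04, rounded up to 77.

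77/0.85 = 90.6, rounded up to 91 per arm, or 182 in total.

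The stated sample size reproduces, so 182 and 15% belong together.

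**2. Participants without the 26-week survey at planned attrition.**

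- In total: 0.15 × 182 = 27.3, leaving 154.7.
- Per arm: 0.15 × 91 = 13.65, leaving 77.35.

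This counts expected non-respondents. It does not count lost events.

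**3. What attrition alone costs in precision.** If an arm reports no events, the exact one-sided 95% upper bound on its rate is 1 − 0.05^(1/n).

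- n = 91: 3.2%
- n = 77: 3.8%

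The loss of numbers matters little. What matters is whether those who leave differ in their events, and the article gives nothing from which to estimate that.

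**4. Recall windows set side by side.**

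| Item | Recall period |
|---|---|
| WOMAC function | prior week |
| Strengthening days | prior two weeks |
| Co-interventions | prior month |
| Adverse events | up to 26 weeks (inferred: asked once, at the end) |

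The article does not print the recall period of the adverse-event questions. The 26 weeks follows from there being a single asking time. Adverse events have by far the longest window among these items.

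**5. Attribution, by assumption only.** No event rate or capture fraction is in the article. Suppose a true rate of 10% in both arms.

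| Share captured, arm 1 / arm 2 | Reported rates | Apparent risk ratio (arm 2 / arm 1) |
|---|---|---|
| 100% / 100% | 10% / 10% | 1.0 |
| 50% / 50% | 5% / 5% | 1.0 |
| 50% / 80% | 5% / 8% | 1.6 |
| 80% / 50% | 8% / 5% | 0.63 |

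Equal under-capture lowers both rates and leaves the ratio intact. Unequal capture creates a ratio with no true difference, in either direction.

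**6. What a 14-week item would recover.** For events before week 14, the longest recall falls from 26 to 14 weeks. Events after it fall within the last 26 − 14 = 12 weeks. For people lost between weeks 14 and 26, it recovers events up to week 14 only. For people lost earlier, it recovers nothing. How the 27 would split between these groups is not stated.

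**The case against.** The strongest defence is that this is a deliberate and explicit choice. The definition is taken from another of the group's trials, it is applied identically and at the same time in both arms, the interventions are low-risk, and no planned between-group test uses adverse events. That stands, and it limits the point to an improvement in safety ascertainment.

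Four stronger readings are tempting, and the article does not support them.

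- **A serious event could stay unknown until the final survey.** The article mentions an internal trial protocol document. Expedited and spontaneous reporting is what an article commonly leaves to such a document.
- **The 27 leave no adverse-event record at all.** Withdrawal procedures are likewise commonly left to the full protocol, so 27 is only the planned number without the 26-week survey.
- **The app pushes people beyond the exercise arm's programme.** Both arms have the same programme, three times a week at the same target intensity, and app users are told to set a goal of three sessions. One example message suggests making the exercises harder, but it answers a particular barrier that the user selects, and both arms are advised how to progress on their own. Adherence may differ between arms, so a safety question remains, but a weaker one.
- **The counts are shown to be biased by a known amount.** Under-capture is a plausible consequence of the design. Its size, and the direction of any difference between arms, are not known.

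The objection that all-cause counting is not obviously better also has force. Eligibility requires knee pain on most days, so counting any two-day increase in pain would include much ordinary osteoarthritis fluctuation. It should supplement the attributed count, not replace it.

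**Conclusion.** The point holds as a risk to the descriptive safety comparison. The text fixes one survey at 26 weeks and a causal judgement by unblinded participants as a condition of counting, although a 14-week questionnaire already reaches both arms. At planned attrition about 27 of 182, roughly 14 per arm, would not answer it. Loss through recall and attribution cannot be sized, and the ratios above are illustrations. The conclusion assumes that the schedule not shown adds no adverse-event item at another time. The primary analyses are unaffected. The change is worth making because it is cheap and uses a contact that the trial already has.

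**What to change.** 1. From a single calendar date, add the same adverse-event items to the 14-week questionnaire in both arms. Do not use the app arm's monthly survey for this, because ascertainment would then differ by arm.
2. Ask first whether any problem met the severity criterion (two days or more of increased pain or disability, or treatment sought). Then ask separately whether the participant thinks it resulted from the trial. The current definition is recovered as yes to both.
3. Keep the 26-week participant-attributed count as the main figure, so that one definition and one time point cover all participants.
4. Report the week-14 counts and the all-cause counts by arm as supplementary, with the number assessed per arm at each time.

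The cost is a minor amendment and a slightly longer survey. The all-cause count will contain flares unrelated to the trial. Recruitment began in August 2021, so participants already past week 14 at the change will have no week-14 data, and neither will those lost before it. This is why the new counts are supplementary.
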